### Trial design {8}

This is a researcher-blind, parallel group randomised controlled superiority trial with two arms. Eligible participants will be randomised in a 1:1 allocation ratio to receive either support from a Community Navigator in addition to routine care (treatment arm), or a booklet with information about local groups and resources plus routine care (control group).

Assessments will be conducted by blinded researchers at the time of consent (baseline) and at two main outcome points: 8-month (end-of-treatment) and 14-month (6 months after end-of-treatment). Baseline measures will be collected at the screening visit, or may be completed if necessary in subsequent meetings, within a maximum of 4 weeks from taking consent. Additional depression and loneliness ratings will be collected through a self-completed online form or through a phone or video call with a study researcher at 4 and 11 months. These additional 4- and 11-month data collection points will be used in additional analyses exploring mediating effects of loneliness on depression (see section “Methods for additional analyses (e.g., subgroup analyses) {20b}”).

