### Intervention description {11a}

#### The intervention

The Community Navigator programme was co-produced with service users and practitioners [7]. It is designed to increase social connections and reduce feelings of loneliness for people with TRD using secondary mental health services.

The programme offers participants up to 10 sessions of 1:1 support from a Community Navigator and attendance at three participant group “meet-ups” over a 6-month period. Participants are then offered one follow-up phone call and attendance at one more meet-up group during the next 2 months, so the intervention is concluded within 8 months from randomisation. Participants must attend at least three individual sessions with the Community Navigator for the intervention to be considered to be delivered per protocol. It is designed to be delivered primarily through face-to-face contact, but 1:1 and participant group “meet-ups” could all be arranged remotely if required to meet participants’ needs and preferences. To help develop social connections as part of the goals of the intervention, participants will be able to access modest financial re-imbursement to cover costs incurred (a maximum of £100 per participant). This will help ensure that poverty, or delays with personal budgets or other forms of statutory assistance, are not insuperable barriers to enacting goals to address loneliness. A detailed intervention manual was developed during the completed feasibility trial [7] and will guide the Community Navigators and supervisors in this trial.

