
Group meet-ups will have an informal style and be lightly facilitated by the Community Navigators. They will encourage information-sharing about helpful local resources, experiences of developing connections and what has helped. Navigators will also introduce participants who may have shared interests or points of connection, and potentially help facilitate a meeting as part of 1:1 support if participants are keen. Responding to qualitative feedback from the completed feasibility trial, we plan a “soft ending” to the programme which does not feel abrupt. Navigators will offer a telephone or video call follow-up and one more group meet-up (the fourth of four available to each participant) after the ten 1:1 meetings, all to be completed before 8-month follow-up.

Participants will also continue to receive routine care from their mental health team (CMHT). If any treatment group participants are discharged from the CMHT more quickly than anticipated at trial enrolment, while they are still receiving support from a Community Navigator, this support will continue unless the clinical team explicitly direct that this is inadvisable. Local protocols will be developed for Community Navigators to be able to pass on any concerns about participants’ safety or wellbeing to the CMHT, even for participants who have been discharged from the team.

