#### Secondary outcome statistical analysis

The effect of the intervention on secondary outcomes will be assessed using analogous methods to those used for the primary outcome. Most of the secondary outcomes are numerical and hence will be analysed using a similar model to that used for the primary outcome, whereas the binary outcomes (those derived from PHQ-9) will be analysed using a mixed-effects logistic regression model. *P*-values will not be reported for secondary analyses. The number and type of adverse events will be summarised by study arm.

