### Adverse event reporting and harms {22}

Serious adverse events (SAEs) are defined as any event which results in death, is life-threatening, requires hospitalisation or prolongation of existing hospitalisation, or results in persistent or significant disability or incapacity. SAEs will be monitored by researchers through a structured safety monitoring form completed at each follow-up assessment, and through feedback from Community Navigators, participants or involved clinicians at trial sites. Each SAE will be recorded on a case record form. The site Principal Investigator will liaise with the relevant clinical team and the participant if required to assess the event’s seriousness, expectedness and study-relatedness. SAE reports will be sent to the Clinical Trials Unit (delegated by the sponsor) and the DMEC Chair and clinical academic for review. Any serious, unexpected, study-related adverse events (SUSARs) will also be reported to the ethics committee within 7 days of the Chief Investigator becoming aware of them.

Any study-related harms which do not constitute SAEs will also be recorded using CRFs. The study team will also keep a log of any negative feedback or events relating to participants’ involvement in the study, to inform any needs for changes to trial processes or researcher training. These non-serious events will also be reported to the DMEC meetings for external review.

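### By-arm adverse event counts are open to differential ascertainment: navigator feedback is an SAE source in the intervention arm only, and non-serious harms are recorded only if study-related

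*Protocol article*

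**What the plan says.** **Sources of SAEs.** Under Adverse event reporting and harms {22}, "SAEs will be monitored by researchers through a structured safety monitoring form completed at each follow-up assessment", and also "through feedback from Community Navigators, participants or involved clinicians at trial sites". The form, participant feedback and clinician feedback exist in both arms.

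**Who has a navigator.** Trial design {8} describes the arms as "support from a Community Navigator in addition to routine care (treatment arm), or a booklet with information about local groups and resources", with usual care continuing in both. The intervention section gives the extra contact as "up to 10 sessions of 1:1 support from a Community Navigator and attendance at three participant group “meet-ups” over a 6-month period", followed by one call and one further meet-up, all within 8 months of randomisation. It also foresees local arrangements under which navigators are "to be able to pass on any concerns about participants’ safety or wellbeing to the CMHT, even for participants who have been discharged". No counterpart is described for controls.

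**Non-serious events.** Section {22} states: "Any study-related harms which do not constitute SAEs will also be recorded using CRFs". A further log is kept of negative feedback or events, but it too is confined to matters relating to study involvement.

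**Use of the data.** Secondary outcome statistical analysis says: "The number and type of adverse events will be summarised by study arm". No test is stated. Procedure for unblinding {17b} allows the senior statistician, on the DMEC's advice, to be unblinded to examine adverse event differences between groups.

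**The concern.** A by-arm count reflects both how often events happen and how often they are found. Here one arm has an additional finder, in contact for up to 8 months. If the shared channels miss any SAEs, some of those missed will be recovered in the intervention arm and not in the control arm.

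For non-serious events the judgement of relatedness comes before recording. An event in a control participant that nobody links to the study leaves no trace, so a later analysis cannot put it back. Who will be blinded {17a} confirms that participants and care providers know the allocation, so attribution is made with that knowledge.

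At stake is how the safety table is read. A table without a p-value is still read across its columns, by the DMEC and later by readers. An excess in the intervention arm could reflect detection, and a true excess could be dismissed as detection. Without a record of source, neither reading could be checked.

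**Working it through.** The protocol article states no adverse event rate and no capture rate, so there is no figure to reproduce. The check has three parts.

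**1. Channels side by side**

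| Channel | Intervention | Control |
|---|---|---|
| Structured safety form at follow-up | yes | yes |
| Participant feedback | yes | yes |
| Clinician feedback | yes, and navigators may alert the team | yes |
| Navigator feedback | yes | no |

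The asymmetry runs one way only, so any spurious difference in SAE counts points towards more events in the intervention arm.

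**2. Illustrative size for SAEs**

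Let *s* be the share of SAEs caught by the common channels and *c* the share of the missed SAEs caught by navigators. With equal true rates and channels acting independently, the expected reported ratio (intervention to control) is

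ratio = [*s* + (1 − *s*)*c*] / *s*.

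Both *s* and *c* are assumptions.

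| *s* | *c* = 0.25 | *c* = 0.50 | *c* = 0.75 |
|---|---|---|---|
| 0.60 | 1.17 | 1.33 | 1.50 |
| 0.70 | 1.11 | 1.21 | 1.32 |
| 0.80 | 1.06 | 1.13 | 1.19 |
| 0.90 | 1.03 | 1.06 | 1.08 |
| 0.95 | 1.01 | 1.03 | 1.04 |
| 1.00 | 1.00 | 1.00 | 1.00 |

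For example, *s* = 0.70 and *c* = 0.50 give (0.70 + 0.15)/0.70 = 1.21.

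In counts, take 153 per arm (Sample size {14}) and an assumed true SAE risk of 10%:
- *s* = 0.90, *c* = 0.50: control 153 × 0.10 × 0.90 = 13.8; intervention 153 × 0.10 × 0.95 = 14.5.
- *s* = 0.60, *c* = 0.75: control 153 × 0.10 × 0.60 = 9.2; intervention 153 × 0.10 × 0.90 = 13.8.

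These ratios apply while navigators are in contact. If events were spread evenly over 14 months and navigators contributed for 8, the excess would shrink by 8/14 = 0.57, so 1.50 would become about 1.29 and 1.21 about 1.12.

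If the table uses common channels only (*c* = 0), the ratio is 1.00 for every *s*.

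**3. Whether common capture can be taken as complete**

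The form depends on a follow-up assessment taking place, and Sample size {14} assumes 15% attrition. The 4- and 11-month data may come from a self-completed online form. Table 1 allows the 8-month visit to be up to 3 months late. Table 1 also marks active adverse event monitoring at screening, 4 and 8 months, and adverse event review at those points and 11 months. It marks neither at 14 months, whereas section {22} has the form completed at every follow-up assessment. Complete capture is therefore possible but not assured.

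For non-serious events no ratio can be computed, because the document gives nothing on how often events would be judged study-related in either arm.

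**The case against.** The strongest counter-argument is that SAEs here are defined by hard criteria: death, threat to life, hospitalisation, lasting disability. Both arms get the same structured form, follow-up interviewers are blinded, and clinicians can report in both arms. People due for discharge from the team within 8 months are excluded, so a clinician is normally in place for both arms during the programme. Most events that a navigator hears of may reach the form anyway. This stands, and it limits the size: at 90–95% common capture the ratio is 1.01 to 1.08.

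The relatedness filter is worded identically for both arms, and controls also undergo consent, screening and repeated assessments that could cause study-related harm. Fewer related harms under a booklet may be a true difference. This also stands: the filter is unequal only through attribution.

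The by-arm summary is descriptive, and each SAE is individually assessed and reviewed. That lowers the stakes without making the counts comparable.

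It can be said that table layout and form fields belong to the SAP and CRFs, which are not shown. But the reporting sources and the relatedness filter are collection rules stated in the protocol article, and an SAP cannot separate sources that were not captured.

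A reader might infer that the comparison is biased by design, that the intervention arm will show more SAEs, or that nearly all non-serious harms will fall there. The documents do not support this. They give no capture or attribution rates, and the SAE bias vanishes if the common channels are complete. Nor is the navigators' route to the clinical team itself an SAE recording procedure; it can affect SAE counts only indirectly, through a clinician's report.

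**Conclusion.** The point holds as a risk of differential ascertainment, not as demonstrated bias. The direction for SAEs follows from the stated collection rules: over-counting in the intervention arm. For non-serious harms the same direction is likely, but it rests on attribution being easier for an active, unblinded programme.

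The size is not derivable from the protocol article. The range of about 1.01 to 1.50 depends wholly on assumed common capture of 60–95%, assumed navigator recovery of 25–75% of the remainder, independent channels and equal true rates. The upper end needs poor common capture, and the ratio is 1.00 if capture is complete. Collecting navigator reports is reasonable in itself; the weakness is mixing them, unlabelled, into a summary by arm. This is a low-cost improvement to the safety reporting and does not touch the primary analysis.

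**What to change.** 1. Add a reporting-source field to the SAE form, allowing more than one source per event.
2. State that the by-arm summary uses channels common to both arms: the structured safety form, supplemented by the mental health records and the CSRI hospital-use items already collected in both arms for the economic analysis. The records cover mental health services only. The CSRI looks back 6 months, so the 8-month questionnaire does not reach the first 2 months. Neither replaces the form.
3. Fix one observation period for everyone in that summary, and reconcile Table 1, which marks no adverse event monitoring or review at 14 months, with section {22}.
4. List separately, and describe as not comparable between arms, the SAEs known only through navigators and the study-related non-serious harms.
5. Keep navigator reporting unchanged for safety purposes.

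Participant and clinician feedback also exist in both arms, but a clinician's report may have been prompted by a navigator. With the source field in place, such events can be shown in a supplementary table.

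The cost is one form field and a few sentences in the protocol and SAP. For SAEs already reported, the source would have to be recovered from existing paperwork. The downside is that the comparative table holds fewer events, although every event is still reported.

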### Frequency and plans for auditing trial conduct {23}

Formal audits of trial procedures and data management may be conducted by the sponsor or the Clinical Trials Unit on behalf of the sponsor at any point during the study.

### Plans for communicating important protocol amendments to relevant parties (e.g. trial participants, ethical committees) {25}

Any proposed changes to the trial protocol will be reviewed and approved by the Clinical Trials Unit, the sponsor and the funders, then submitted for approval from the Research Ethics Committee (REC). No protocol amendments will be implemented until REC approval and site approval are then confirmed.

The funders will be informed of new protocol versions so an up-to-date version of the protocol is available on the funders’ website.

### Dissemination plans {31a}

This study is funded by the English National Institute for Health and Care Research, Health Technology Assessment Programme (NIHR HTA). It has been added to the NIHR Clinical Research Network Portfolio and included on the ISRCTN registry.

Our study will provide high-quality evidence about the effectiveness of a novel programme to address loneliness and social isolation and reduce depression for people with TRD in secondary care. We will provide a final report for the funders in adherence to their requirements. We will seek to publish scientific papers in open access journals, reporting the trial protocol, main results, qualitative investigations and health economics findings. In collaboration with the trial Lived Experience Advisory Panel members, we will co-produce a briefing document for policy makers, a guide to support future programme delivery in mental healthcare settings, and articles in publications read by practitioners and commissioners and by service users and the public. We will present findings at stakeholder workshops, meetings or conferences. We will update the Community Navigator intervention manual and training manual and make these publicly available, to speed up knowledge transfer if warranted by trial findings.

The Study CI will draft a publications plan identifying proposed lead and included authors and timescales for publications. This will be discussed and agreed at study TMG meetings. Authorship will be based on ICMJE guidelines. All proposed publications will be discussed with and reviewed by Priment CTU prior to publishing.

Trial participants will be asked during the consent process if they would like to receive a lay summary of the study findings. The study team will work with the trial Lived Experience Advisory Panel to develop an accessible summary of the study findings to send to all interested participants when the study is over.

## Discussion

Our trial addresses a gap in evidence regarding theory-driven and potentially effective social interventions for people with TRD that, by targeting loneliness and social isolation, would act via a different mechanism from the pharmacological and psychological treatments currently available. Our intervention could help mental health services provide genuinely biopsychosocial care for an important clinical group who are not adequately helped by current treatments.

Research on interventions for loneliness in mental health is in its infancy: effective models of support have yet to be established [17]. The Community Navigator programme represents one socially focused approach to addressing loneliness, involving employing additional staff with a bespoke role solely to help people with social connections, in addition to usual care. Other studies have developed and tested social interventions with different mental health client groups which involve seeking to train and upskill the existing care team [48]. A range of psychological interventions for loneliness has also been developed [49]. Whatever the result of our trial, further research is required to determine the most acceptable and effective intervention models to reduce loneliness and improve health and social outcomes across a range of clinical groups. To our knowledge however, the Community Navigator trial is the first study of a programme designed to reduce depression through alleviating loneliness for people with TRD in a secondary care context. Findings will provide rich information to inform practice and future research.

## Trial status

The current trial protocol is Version 4.0, 7th July 2023. The first trial participant was recruited on 7th September 2022. Participant recruitment is currently due to be completed by April 2024.

## Data Availability

The Community Navigator programme intervention manual and training manual will be made publicly available on the study website at the need of the trial. All requests for the participant-level dataset and statistical code should be submitted to the corresponding author for consideration. Access to anonymised data may be granted following review, involving the trial statistician and Priment Clinical Trials Unit team.

## Abbreviations

CMHT: Community Mental Health Team
CIS-R: Clinical Interview Schedule-Revised
CRF: Case report form
CRN: Clinical Research Network
CSRI: Client Service Receipt Inventory
DJG-6: 6-Item De Jong Gierveld Loneliness Scale
DISC: Discrimination and Stigma Scale
DMEC: Data Monitoring and Ethics Committee
EQ-5D-5L: EuroQol EQ-5D 5 level (EQ-5D-5L)
EU: European Union
GAD-7: General Anxiety Disorder Assessment
GAfREC: Governance Arrangements for NHS Research Ethics
GCP: Good Clinical Practice
GDPR: General Data Protection Regulation
HRA: Health Research Authority
ICD-10: International Classification of Diseases 10th Revision
ISRCTN: International Standard Randomised Controlled Trial Number
LEAP: Lived Experience Advisory Panel
LSNS-6: Six-item Lubben Social Network Schedule
MIS: Four-item Multiple Identities Scale
NIHR HTA: National Institute of Health Research Health Technologies Assessment Programme
PHQ-9: Patient Health Questionnaire – Mental Health Disorders
QALY: Quality-adjusted life year
QPR: Questionnaire on the Process of Recovery
RCT: Randomised controlled trial
REC: Research Ethics Committee
REQOL: Recovering Quality of Life
B-RSES: Brief Rosenberg self—esteem scale
SAE: Serious adverse event
SDV: Source Document Verification
SOP: Standard Operating Procedure
SUSAR: Suspected unexpected serious adverse reaction
TMG: Trial Management Group
TRD: Treatment-resistant depression
TSC: Trial Steering Committee
ULS-8: University Of California, Los Angeles Loneliness Scale
